**Figure 1 f1:**
[figure not shown]
Multistate model describing the transitions between different clinical states.

### Confounder variables

The list of confounder variables is presented in table 1. To account for heterogeneity across ICUs, all models will include random effects for each unit.

**Table 1 t1:** List of confounder variables. In addition to these variables, all models will contain a random intensive care unit variable

Variable	Time of recording
Number of days on oral nutrition	Days 0 - 2 post ICU admission
Number of days on parenteral nutrition	Days 0 - 2 post ICU admission
Number of days with protein intake > 1.2g/kg day	Days 0 - 2 post ICU admission
Year of therapy	Admission date
APACHE II score	ICU admission
Main admission diagnosis*	ICU admission
Admission category (surgical elective/emergency, medical)	ICU admission
Age	ICU admission
Sex	ICU admission
BMI	Pre-ICU admission
Baseline number of days under MV†	Days 0 - 2 post ICU admission
Number of days under MV before state transition‡	Days 0 - 11 post ICU admission

ICU – intensive care unit; APACHE - Acute Physiology and Chronic Health Evaluation; BMI - body mass index; MV - mechanical ventilation.

* Gastrointestinal, cardio-vascular, metabolic, neurologic, orthopedic/ trauma, renal, pulmonary, sepsis, other. Sepsis was the main admission diagnosis, if there was an infection-associated circulatory dysfunction requiring vasopressor therapy which dominated dysfunction of other organs;

† only used when analyzing the association of daily propofol-associated energy intake (categorized variable) with time-to-discharge alive/in-hospital death (cumulated for the early and late phase after intensive care unit admission);

‡ only used in multistate models

### Outcome measures

–**Primary outcomes:** time-to-hospital discharge-alive as a surrogate of morbidity, and to in-hospital death (adjusted hazard ratios and 95% confidence intervals [95%CI]).Adjusted hazard ratios compare two levels of daily propofol-associated energy intake. They will be calculated separately for each day after ICU admission using sub-distributional and cause-specific hazard models. The observation period will start on the day of ICU admission, and events (day of discharge alive/in-hospital death) will be registered from day 2 after ICU admission until the end of the lead-time (defined as twice the number of days that a patient received propofol therapy).–**Secondary outcomes:** the risk of state transition (adjusted hazard ratio and 95%CI) and the transition probabilities between the different states (Figure 1).State transition risks and probabilities will be referred to a certain amount of propofol-associated energy intake or a specific duration of propofol therapy; adjusted hazard ratios will be calculated for all 17 transitions (Figure 1). State transition will be registered until day 13 after ICU admission. Initial and absorbing states include "propofol: no/MV: no", "propofol: yes/MV: no", "propofol: no/MV: yes", "propofol: yes/MV: yes", post-transition absorbing states include "in-ICU death" and "ICU discharge alive.

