#### Data collection

Using a secure web-based data collection tool, the following information was collected: date of ICU admission, admission category (elective surgery, emergency surgery, and medical), primary admission diagnosis (nine categories), sex, age, BMI, daily use of MV/propofol therapy, and Apache II score on the day of admission. Attending physicians or allied healthcare professionals with expertise in nutrition practices (e.g., dietitians) also recorded daily protein intake and route of additional caloric intake (enteral nutrition, parenteral nutrition). For the first 11 days after ICU admission, the database contains information on protein and energy intake, as well as the number of days on which a patient received parenteral nutrition or oral feeding at any time.

Daily propofol-associated energy intake was also collected from the day of ICU admission (partial day) to a maximum of 11 additional days after admission. Information on the exact dose of propofol (administered via 1% or 2% solutions) was not available in the database. However, as propofol-associated energy intake is closely related to the dose of propofol, propofol-associated energy intake can be used as a surrogate parameter for this dose (1mL of a solution containing propofol contains 50mg of soybean oil, and 50mg of purified egg phosphatide, equivalent to 1.1kcal/mL).

Patients were followed in the hospital for a maximum of 60 days after ICU admission. We recorded the time to in-hospital death or discharge alive. Patients who remained alive in the hospital for more than 60 days were considered censored for both risks at that time.

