#### Sample size considerations

The large number of patients in the database (more than 18,000 with an ICU LOS > 2 days) will be sufficient to support advanced, in-depth statistical analyses. In this subgroup, the 60-day hospital discharge alive rate is approximately 70%, resulting in more than 10,000 events (discharges).^(15)^ Considering the number of planned predictor parameters (confounders, see below), the events per predictor parameter ratio will be large enough to perform reliable complex statistical analyses.^(16)^

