### Overall design of the competing risk models used to analyze time to discharge alive and to in-hospital death

The primary aim will be to analyze the association between daily propofol-associated energy intake from day 1 to day 11 after ICU admission and the time to the hospital endpoint (discharge alive with in-hospital death as a competing risk).

Recording of propofol-associated energy intake was stopped if a patient died, was discharged from the ICU, or was in the ICU for more than 11 days. However, our statistical model requires information on propofol-associated energy intake on propofol days 1 to 11 after ICU admission for all surviving patients, even if patients were discharged from the ICU before day 11. Assuming no propofol-associated energy intake after ICU discharge alive, we will impute a daily propofol-associated energy intake of 0 for these patients.

To account for the fact that a short duration of propofol therapy (and propofol-associated energy intake) may not affect outcome over a more extended period, we will use a lead-time defined as twice the number of days that a patient received propofol therapy. These lead times provide a window in which propofol-associated energy intake on a given day could have affected the subsequent day of discharge alive (time to discharge alive).

To facilitate the interpretation of the associations between propofol-associated energy intake and outcome estimated by our model, we will construct five different hypothetical propofol-associated energy intake use patterns (reflecting three different levels of daily propofol-associated energy intake (low, medium, high) on propofol days 1 to 11). These levels of use will also be used to model associations between propofol-associated energy intake and outcomes. Similar to our recent publications,^(9,15)^ we will distinguish between an early (days on propofol #0 to #4) and a late (days on propofol #5 to #11) acute phase.

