We will then use these models to compare the expected outcomes of hypothetical propofol-associated energy intake patterns, controlling for confounders. We will design six different pairwise comparisons of these artificial patterns, analyzing the events of interest (separate models for early acute phase, late acute phase, or early + late acute phase: comparison of intermediate propofol-associated energy intake *versus* low propofol-associated energy intake, and high propofol-associated energy intake *versus* intermediate propofol-associated energy intake). All adjusted hazard ratios (pairwise comparisons of different hypothetical propofol-associated energy intake patterns) will be calculated assuming ceteris paribus.

The primary objective of the analysis of propofol-associated energy intake is to obtain the cumulative incidence function of the events of interest (time-to-discharge alive, taking into account the competing event of in-hospital death). We will again use PAMM. We will use techniques employed in previous publications^(9,15)^ to model cumulative effects where past values of a propofol-associated energy intake influence the hazard on a given day after ICU admission. This is relevant when accumulated propofol exposure may increase the risk of an event.

To model the cumulative effects over the follow-up period, we will use the lead time described above. This describes the time interval during which a propofol-associated energy intake registered on a given day after ICU admission affects the likelihood of hospital discharge alive or in-hospital death. We will first create the piecewise exponential data format by constructing covariate matrices for propofol-associated energy intake, additional matrices representing the time of exposure, and a lead matrix defining the time window during which the event of interest (hospital discharge alive or in-hospital death) will be recorded. Furthermore, we will divide the time axis after ICU admission into segments (Day x to Day x + 1 after ICU admission), assuming a constant exponential distribution within each segment.

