Propofol-associated energy intake is a time-dependent covariate characterized by time-varying exposure. This time-varying exposure can be described by an individual's exposure history, in which a specific value of propofol-associated energy intake is attributed to each day after ICU admission. To model the cumulative associations, we will first compute the partial association over the time window containing the aforementioned segments, in which the value of propofol-associated energy intake on a given day after ICU admission can affect the hazard rates. For cumulation, we will use the weighted cumulative exposure model,^(28)^ in which the partial associations are assumed to be linear and depend only on the time window. This model is defined as the definite integral of the partial associations over the entire time window. Furthermore, the model computes the cumulative associations between time-varying propofol-associated energy intake and recency.

For the primary analysis, we will first fit cause-specific hazard models for each event type, and then combine the resulting models to estimate the cumulative incidence function for each event type.^(15)^ The cumulative incidence function is calculated by considering the probability of hospital discharge alive or in-hospital death until the end of the lead time. For comparison, we will also use the Fine–Gray subdistribution hazard model to analyze predictors (including the cumulative association of propofol-related energy intake) of time-to-discharge alive.^(29)^

The Fine-Gray model is a type of proportional hazards model used to estimate the probability of the event of interest (hospital discharge alive) occurring, while accounting for in-hospital death (a competing risk), which can prevent a patient from being discharged alive from the hospital. The Fine-Gray model directly estimates the cumulative incidence function of the cause of interest (discharge alive), and the advantage of this model is that the effects of covariates and exposures can be interpreted directly with respect to the cumulative incidence function. The general estimation approach will be equivalent to the cause-specific approach described above; however, there will be no need to model the competing event directly.

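### The primary event window is tied to each patient's own number of propofol days, and conflicts with the 60-day follow-up and with the lead time's other description

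*Protocol article*

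**What the plan says.** Three statements tie the event window to the patient's own propofol days:

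- Outcome measures: observation starts on the day of ICU admission. Events "will be registered from day 2 after ICU admission" and counting continues "until the end of the lead-time (defined as twice the number of days that a patient received propofol therapy".
- Overall design of the competing risk models repeats the definition ("we will use a lead-time defined as twice the number of days that a patient received propofol therapy") and builds "a lead matrix defining the time window during which the event of interest (hospital discharge alive or in-hospital death) will be recorded".
- The same section fixes the horizon of the curves: "The cumulative incidence function is calculated by considering the probability of hospital discharge alive or in-hospital death until the end of the lead time".

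Other statements point elsewhere. The competing-risk section also says of the lead time: "This describes the time interval during which a propofol-associated energy intake registered on a given day after ICU admission affects the likelihood". That describes how long an exposure acts, not how long a patient is observed. Data collection has a common horizon: "Patients who remained alive in the hospital for more than 60 days were considered censored for both risks at that time". Sample size considerations count events over that horizon: "the 60-day hospital discharge alive rate is approximately 70%, resulting in more than 10,000 events (discharges".

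The inclusion criteria (age, BMI, ICU stay) do not require propofol, and the lowest intake level in the Descriptive analysis section, below 1.0 kcal/kg per day, includes zero. The lag-time sensitivity analysis shortens the window by two days. The article gives no rule for a patient with zero propofol days.

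**The concern.** In a time-to-event analysis, the period at risk should not be set by the exposure under study, least of all by exposure that has not yet happened. If events count only up to twice the patient's own propofol days, three things follow. Non-users drop out of the comparison. Late events are lost for everyone. A patient with little propofol so far stays in the early risk set only if he lives, and stays in the ICU, long enough to receive more. The last is immortal time: event-free days are credited to low prior exposure, while early deaths and discharges at low exposure are not counted. The apparent result is more events with more propofol, even if propofol does nothing. The study's general aim is evidence on safe dosing and duration, so a false dose-response for death would be a serious outcome.

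**Working it through.** **Reading used.** The window runs from day 2 to day 2n, counted from ICU admission, with n the patient's total propofol days. Intake is recorded on days 0 to 11, so n is at most 12.

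**1. The article's own event count.** 18,000 × 0.70 = 12,600 discharges, consistent with its statement of more than 10,000. This is a 60-day count.

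**2. Window ends.**

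| n | Last event day (2n) | Event days open, of the 59 on days 2-60 | Last event day with two-day lag (2n − 2) |
|---|---|---|---|
| 0 | 0 (before day 2) | 0 | none |
| 1 | 2 | 1 | 0 (none) |
| 3 | 6 | 5 | 4 |
| 5 | 10 | 9 | 8 |
| 12 | 24 | 23 | 22 |

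Never-users cannot contribute an event, and everything on days 25 to 60 is excluded for every patient.

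**3. Dependence on the future.** Take two patients with no propofol by day 4. One dies that day: n = 0, no window, death not counted. The other starts on day 6 and receives five days: n = 5, the window ends on day 10, and days 2 to 5 are credited as event-free time at zero prior exposure. Late starts are expected, because the multistate model includes moves from no propofol to propofol.

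**4. Size under a null.** The simulation had 100,000 patients per scenario, with constant daily hazards (death 0.010, discharge 0.035) unrelated to propofol. A Poisson piecewise-exponential model with a daily baseline gave the hazard ratio per propofol day before the event day. The shares of never-users and late starters and the mean course length are assumptions.

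| Never / late start / mean days | Death, 2n window (95% CI) | Discharge, 2n window (95% CI) | Death; discharge, 60 days |
|---|---|---|---|
| 20% / 0% / 5 | 0.994 (0.967-1.022) | 1.001 (0.986-1.016) | 1.003; 0.999 |
| 20% / 20% / 5 | 1.164 (1.139-1.188) | 1.178 (1.165-1.192) | 1.005; 1.000 |
| 20% / 40% / 5 | 1.250 (1.225-1.275) | 1.264 (1.251-1.278) | 0.997; 1.001 |
| 40% / 20% / 3 | 1.308 (1.256-1.363) | 1.288 (1.261-1.316) | 0.999; 0.997 |

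**5. Events retained.** The article gives neither the distribution of propofol days nor that of discharge times. The grid assumed a median discharge day of 10 to 25, 0-40% never-users, and a mean of 3 to 8 propofol days among users. The window then kept 2% to 70% of 60-day discharges, and less than half in 33 of 36 scenarios. Applied to 12,600, that is 252 (0.02 × 12,600) to 8,820 (0.70 × 12,600).

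**The case against.** The strongest reply is that the lead time is only an effect window. The competing-risk section says so more than once, the weighted cumulative exposure model needs such a window, and follow-up is censored at day 60. Never-users would then stay at risk with no exposure contribution, and nothing would be truncated. The modelling technique is also deferred to earlier publications that are not available here. This is a fair reading of those sentences, but it does not fit the primary outcome definition or the horizon of the cumulative incidence, both of which stop at the lead time. It shows a contradiction rather than removing one.

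The literal reading also rests on two premises that the article does not state. If n were a running count, risk-set membership would not depend on future exposure and step 3 would fall; zero propofol days would still leave no window. If the window ran from the last propofol day, its latest end would be about day 35 (11 + 24), still short of day 60, and a never-user would have no starting point.

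A reader might go further than the documents allow in four ways:

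- **Most 60-day events are discarded.** This is likely under many assumptions, but it cannot be derived. The only duration figure in the article, a median of 2.6 days, is interventional sedation in a cited randomized study, not this cohort.
- **The primary hazard ratios are certainly biased.** The first simulation row shows no bias when all users start on day 0 and duration is unrelated to risk.
- **The simulated ratios measure the error in the planned result.** They are per prior propofol day. The planned contrasts compare levels of daily kcal/kg in a weighted cumulative exposure model.
- **The study is too small, or the low-intake curve has no horizon.** The retained count is too uncertain to judge the first. As to the second, the low level also includes non-zero intake, so a hypothetical low pattern need not mean zero propofol days.

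**Conclusion.** The point holds in this form. The article gives the lead time two incompatible roles, as the limit of event registration and as the reach of a day's intake, and neither the primary outcome nor the cumulative incidence is reconciled with the 60-day follow-up. Under the literal rule (window from ICU admission, n the total), three consequences need no simulation: no event window for eligible patients without propofol, no event after day 24 for anyone, and a risk set that depends on propofol still to come. The count of 12,600 discharges therefore does not describe the primary analysis.

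The size of any bias is conditional. It is material if an appreciable share of patients start late and absent in the day-0-start case. The ratios show direction and plausible strength; they do not forecast the planned estimates. Because the defect lies in the risk set of the primary outcome, it should be settled before analysis.

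**What to change.** - Reconcile Data collection, Outcome measures and the competing-risk section, so that the lead time has one meaning and no longer ends follow-up.
- Follow all patients, never-users included, for both events to day 60.
- Use lag and lead only inside the exposure weight function. Make them depend on the exposure day alone, identical for all patients, with a length fixed in advance, and let only intake recorded before the event day enter.
- Report cumulative incidence at fixed days common to all patients, for example 30 and 60.
- Restate the event count in Sample size considerations for the window actually analysed.

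The cost is revised wording and a changed lead matrix; no new data are needed. The downside is that the fixed lead length must be justified, with sensitivity to one or two other values shown.

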### Data management plan

All data collected during the study were recorded by designated site personnel in a dedicated repository and stored in a study-specific database.^(17)^ Data from this database were transferred to an electronic data management system that complies with the guidelines for Good Automated Manufacturing Practice, version 5.0 (GAMP 5; INES, IQVIA, Paris, France). All patient data are pseudonymized and coded with a unique patient identification (ID) number generated by the electronic data management system. The database complies with all applicable national, regional, and local regulations on patient data protection and record keeping. Data analysis will be performed using R statistical software. Details of the study will be reported in accordance with the Strengthening the Reporting of Observational Studies in Epidemiology (STROBE) guidelines.

### Statistical analysis plan

#### Descriptive analysis

Continuous variables are described by mean, SD, median, minimum, and maximum values. In addition, two-sided 95%CIs are calculated for continuous variables. Additional descriptive statistics may be calculated as needed (e.g., quartiles, coefficient of variation, etc.). In particular, the median and interquartile range (IQR) are used to describe non-normally distributed data. Frequencies and corresponding percentages per class level describe categorical variables. Patients with missing data will be excluded. However, we will examine where and how frequently missing values occur in the data overall, how often they co-occur across variables, and whether there are notable patterns of missingness across groups. We will then derive possible limitations of this study from that analysis.

For the competing risk analyses (time-to-discharge alive, time to in-hospital death), we will classify daily propofol-associated energy intake using three thresholds that define three different levels based on the amount of propofol-associated energy received. The identification of specific energy thresholds will be based on clinical practice:^(18,19)^ level I: < 1.0kcal propofol-associated energy/kg per day; level II: 1.5 - 4.5kcal propofol-associated energy/kg per day; level III: > 4.5kcal propofol-associated energy/kg per day). Suppose there is a highly uneven distribution of patient days with a given level of propofol-associated energy intake. In that case, energy thresholds may be redefined after preliminary exploratory analysis of these data, but before assessing the association with outcome.

For converting propofol-associated energy intake into mg propofol, we will assume that the use of 1% and 2% propofol in the present study was similar to that in the multinational EuroPN study on medical nutrition therapy (2% propofol: 62%, 1% propofol: 37%, unknown: 1%; unpublished observations of the EuroPN study).^(20)^ From these data, it is possible to convert propofol-associated energy intake into mg propofol. According to Appendix A, the energy levels above would roughly correspond to the following propofol dose levels: level I: < 20mg/kg per day; level II: 20 - 60mg/kg per day; level III: > 60mg/kg per day. These propofol categories, however, will only be used to interpret results. For all statistical analyses, we will use the levels defined above based on propofol-associated energy intake.

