### Subgroup analysis

In order to look at associations according to admission diagnosis, sex and age, the results will be analyzed separately for female patients, surgical patients with a cardio-vascular admission diagnosis, patients who only had a low propofol-associated energy intake during the first 48 hours after ICU admission (daily propofol-associated energy intake (level I): < 1.5kcal/kg per day), patients younger than 65 years and patients with an admission APACHE II score ≥ 25.

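### The exposure levels leave 1.0 to <1.5 kcal/kg per day unassigned, and level I has two different upper bounds

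*Protocol article*

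**What the plan says.** All of this is in the protocol article.

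- **Descriptive analysis, energy levels.** Daily intake is to be classified "using three thresholds that define three different levels based on the amount of propofol-associated energy received". The levels are "level I: < 1.0kcal propofol-associated energy/kg per day; level II: 1.5 - 4.5kcal propofol-associated energy/kg per day" and "level III: > 4.5kcal propofol-associated energy/kg per day".
- **Descriptive analysis, dose equivalents.** Through Appendix A, the same levels are said to correspond roughly to "level I: < 20mg/kg per day; level II: 20 - 60mg/kg per day", with level III above 60 mg/kg per day. These mg bands are for interpretation only; every statistical analysis is to use the energy levels.
- **Subgroup analysis.** Patients with only low intake in the first 48 hours are identified by "daily propofol-associated energy intake (level I): < 1.5kcal/kg per day".
- **Where the levels are used.** Table 2 lists categorized daily intake as the exposure for the primary outcome. The section on the competing risk models says the levels serve to model the associations as well as to build the hypothetical intake patterns. It plans six pairwise comparisons: intermediate versus low and high versus intermediate, each for the early phase, the late phase and both together.

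**The concern.** A categorized exposure needs a rule that places every possible value in exactly one category. Here level I stops at 1.0 and level II starts at 1.5, so the values between have no category. The Subgroup analysis section would place those same values in level I.

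The broken boundary separates low from intermediate intake, which is one of the two types of contrast planned for the primary outcome. The competing risk model needs an exposure value for each of days 1 to 11 in every surviving patient, so a day without a level has to be dealt with somehow. An analyst could call it level I, call it level II, or treat it as missing. Under the plan's complete-case rule, the last choice could remove the whole patient. The document does not choose among these, and each gives a different low-versus-intermediate comparison. Membership of the low-intake subgroup also depends on which level I is meant.

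**Working it through.** **1. Code the rules as printed** (Descriptive analysis: <1.0; 1.5 to 4.5; >4.5 kcal/kg per day).

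| Intake (kcal/kg per day) | Level as printed | Level I under the subgroup definition (<1.5)? |
|---|---|---|
| 0 | I | yes |
| 0.99 | I | yes |
| 1.0 | none | yes |
| 1.2 | none | yes |
| 1.49 | none | yes |
| 1.5 | II | no |
| 4.5 | II | no |
| 4.51 | III | no |

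**2. Reproduce the conversion factor.** Appendix A takes 1.1 kcal/mL, 20 and 10 mg/mL, and a 2%:1% ratio of 1.8 in mg. Then

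mg per kcal = 1 / [(1.8 × 1.1)/(2.8 × 20) + 1.1/(2.8 × 10)] = 1 / (0.03536 + 0.03929) = 13.40.

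The article states 13.5, which agrees within 1%.

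**3. Convert the cut-points at the stated 13.5.**

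| Energy cut-point | × 13.5 | Stated equivalent | Difference |
|---|---|---|---|
| 1.0 | 13.5 mg/kg | 20 mg/kg | −32.5% |
| 1.5 | 20.25 mg/kg | 20 mg/kg | +1.25% |
| 4.5 | 60.75 mg/kg | 60 mg/kg | +1.25% |

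In reverse, 20/13.5 = 1.48 and 60/13.5 = 4.44 kcal/kg.

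**4. Test whether another conversion rescues 1.0.**

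| Assumption | 1.0 kcal/kg becomes | 1.5 kcal/kg becomes |
|---|---|---|
| mg ratio 62:37 | 13.2 mg/kg | 19.9 mg/kg |
| Ratio of 1.8 read as volume | 14.9 mg/kg | 22.4 mg/kg |
| 1% solution only | 9.1 mg/kg | 13.6 mg/kg |
| 2% solution only | 18.2 mg/kg | 27.3 mg/kg |

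None takes 1.0 to 20 mg/kg.

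**5. Count the thresholds.** Three contiguous levels need two cut-points. The three printed values (1.0, 1.5, 4.5) divide the scale into four intervals, one of them unnamed.

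**6. Width of the gap.** (1.5 − 1.0)/1.5 = one third of the range below level II. In dose terms this is 13.5 to 20.25 mg/kg per day.

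**7. Illustration of reach, on assumed shares.** The document gives no distribution of daily intake. Suppose a share p of patient-days over 11 days lies in the gap. If days were independent, the share of patients with at least one such day would be 1 − (1 − p)^11:

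- p = 2%: 1 − 0.98^11 = 20%
- p = 5%: 1 − 0.95^11 = 43%

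If gap days were fully clustered, so that the same patients had them on all 11 days, the shares would be p itself: 2% and 5%. Positive correlation within patients puts the answer between these extremes.

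**The case against.** The strongest reply is that this is a single wrong digit that the rest of the article corrects. The subgroup definition and the dose equivalents both point to 1.5, and days below 1.0 or at 1.5 and above can be coded without difficulty. That is a fair account of how the error probably arose, and it limits the coding problem to days in the gap and to the question of which level I is meant. It does not settle the matter. The article says that the printed energy levels govern all analyses and that the mg bands are only for interpretation, so neither the bands nor a subgroup definition formally overrides the main text.

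Four further points have some force:

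- **Illustrative percentages.** The 2% and 5% shares are assumptions. Independence is implausible because doses on successive days are correlated and days after ICU discharge alive are set to 0. The 20% and 43% figures therefore probably overstate the number of patients affected.
- **Exclusion of patients.** An intake of 1.2 kcal/kg is observed, not missing, so losing the patient under the missing-data rule is a possible consequence and not a stated one.
- **Number of thresholds.** Three cut-points do appear in the printed rules, so the wording "using three thresholds that define three different levels" is at most a symptom of the same slip.
- **Exploratory step.** The plan allows thresholds to be redefined before outcomes are examined, and tabulating days by level would probably expose the gap. The clause applies only when patient-days are very unevenly distributed, so it does not repair an inconsistent definition.

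**Conclusion.** The concern holds. As printed, intake from 1.0 to just under 1.5 kcal/kg per day has no level, and level I has two upper bounds. The gap covers one third of the range below level II and affects the boundary used in three of the six planned comparisons, as well as membership of the low-intake subgroup.

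The protocol's own arithmetic identifies 1.0 as the odd figure: it converts to 13.5 mg/kg against a stated 20, whereas 1.5 and 4.5 both agree with the stated equivalents within 1.3%. That rests only on numbers in the article.

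The effect on the hazard ratios cannot be sized, because the share of patient-days in the gap is not given. The correction should still be made before analysis, since without it the low-versus-intermediate contrast depends on an unrecorded choice by the analyst.

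**What to change.** Use one contiguous set of levels throughout: level I below 1.5, level II from 1.5 to 4.5 inclusive, and level III above 4.5 kcal/kg per day. Correct the level I bound in the Descriptive analysis section, and write two thresholds there instead of three. Keep the Subgroup analysis section on the same level I.

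The article attributes the thresholds to clinical-practice references, so the authors should confirm that 1.5 is the boundary they intended. It is the value that agrees with both the subgroup definition and Appendix A. If they did intend 1.0, then the start of level II, the subgroup definition and the 20 mg/kg equivalent would all have to change.

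This is an exposure-coding cut-point and does not touch patient management. The change is one line in the text, with no loss of data or power, and should be recorded before exposure is linked to outcome.
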